### 8.2. Analysis sets

**Full Analysis Set (FAS):** According to the basic principles of intention-to-treatment (ITT), all randomized subjects are included in the full analysis set. The primary efficacy evaluation of this study is based on the full analysis set.

**Per Protocol Set (PPS):** All subjects who have completed the treatment prescribed by the protocol or who have not significantly violated the protocol are included in the per protocol set. The exact definition of a serious protocol deviation will be finalized at the time of data auditing, which may include but is not limited to the following circumstances.

- 1) Serious violation of inclusion criteria that affects the efficacy evaluation;
- 2) Treatment that seriously interferes with efficacy evaluation after inclusion;
- 3) Serious violation of medication regimen, with a total dose intensity of  $< 80$ ;
- 4) Poor compliance that seriously affects the efficacy evaluation;

5) Too long medication delaying during the treatment;

6) Lack of primary efficacy index, etc.

PPS is a secondary analysis set for efficacy evaluation.

**Safety set (SS):** All randomized subjects receiving more than one dose of the investigational product and one safety evaluation are included in the safety set. The safety evaluation of this study is based on the safety set.

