#### **Analysis sets**

- **Full Analysis Set (FAS):** According to the basic principles of intention-to-treatment (ITT), all randomized patients are included in the full analysis set. The primary efficacy evaluation of this study is based on the full analysis set.
- **Per Protocol Set (PPS):** All patients who have completed the treatment prescribed by the protocol or who have not significantly violated the protocol are included in the per protocol set. The exact definition of a serious protocol deviation will be finalized at the time of data auditing. PPS is a secondary analysis set for efficacy evaluation.
- **Safety Set (SS):** All randomized patients receiving more than one dose of the investigational product and one safety evaluation are included in the safety set. The safety evaluation of this study is based on the safety set.

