## **2.7 Modification to the statistical analysis in the protocol**

Not available.

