## **3 Analysis Dataset**

At the end of the trial, after data cleaning, the study project team will review the data collected during the trial and delimit the analysis dataset according to the following rules.

- **Full Analysis Set (FAS)**

According to the basic principle of intention-to-treat (Intention-To-Treatment, ITT), all subjects who were randomized were included in the full analysis set. The primary efficacy evaluation for

this study was based on the full analysis set.

Treatment assignment for the Full Analysis Set was based on randomization.

- **Per-Protocol Set (PPS)**

Includes all subjects who completed protocol-specified therapy or who did not substantially violate the protocol. The exact definition of a serious protocol violation will be finalized at the time of data review and may generally include (but is not limited to) the following:

- 1) Significant violation of inclusion criteria, affecting the efficacy evaluation;
- 2) There are treatments that seriously interfere with the efficacy evaluation after inclusion;
- 3) Significant drug regimen violation, total dose intensity < 80%;
- 4) Poor compliance seriously affects the efficacy evaluation;
- 5) Delayed medication for too long during treatment;
- 6) Lack of evaluation of primary efficacy indicators.

The PPS was the secondary analysis dataset for efficacy evaluation, and treatment assignment was based on randomization.

- **Safety Analysis Set (SS)**

Defined as all subjects who were randomized and received at least one dose of trial drug and had one safety evaluation. The safety evaluation for this study was based on the Safety Analysis Set.

The treatment groups of the safety analysis set was based on the drug actually received. For the control group, data analysis will be performed by the investigational group as long as the subjects have received one dose of the test drug.

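### The protocol's safety set needs more than one dose and the SAP's needs at least one; in both documents the per-protocol definition joins its two conditions with *or* where *and* is meant

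*Combined protocol and SAP*

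**What the plan says.** **Safety set.** Protocol 8.2 reads: "All randomized subjects receiving more than one dose of the investigational product and one safety evaluation are included in the safety set". The abstract carries the same sentence: "All randomized patients receiving more than one dose of the investigational product and one safety evaluation are included in the safety set". SAP 3 sets a different threshold: "Defined as all subjects who were randomized and received at least one dose of trial drug and had one safety evaluation". The SAP groups this set by the drug actually taken, and adds for control patients that "data analysis will be performed by the investigational group as long as the subjects have received one dose of the test drug". SAP 2.7, the section reserved for changes to the protocol's statistical analysis, contains only "Not available". Both documents make this set the basis of the safety evaluation.

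**Per-protocol set.** The protocol (8.2 and abstract) takes in those who have "completed the treatment prescribed by the protocol or who have not significantly violated the protocol". SAP 3 has the same structure: "Includes all subjects who completed protocol-specified therapy or who did not substantially violate the protocol". Protocol 8.2 and SAP 3 then list six kinds of serious deviation: eligibility, interfering treatment, dose intensity below 80, poor compliance, long dosing delay and a missing primary outcome. The exact definition is left to data review. SAP 4.1.3 also removes patients whose drug did not match their randomisation.

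**The concern.** Two membership rules, read as written, do not give the set that was evidently intended.

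For safety, the documents disagree about a patient with exactly one dose. That patient is not a random loss. Protocol 5.7.1 stops treatment for intolerable adverse reactions. Protocol 5.4.2 stops medication after emergency unblinding, which is allowed only for a serious event suspected to be drug-related. Protocol 5.5 puts at least 6 hours between the first and second tablets, so an acute reaction can end treatment at one dose. Protocol 1.3 lists allergic reactions and shock for edaravone, so any loss would be expected mainly on the active arm. Excluding such a patient removes an event from the numerator of the rate that the set exists to estimate.

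For the per-protocol set, *or* means that either condition is enough. SAP 4.3.1 asks for further exploration where the full-analysis and per-protocol results disagree. That comparison says little about violations if violators who completed treatment stay in.

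**Working it through.** **1. The plan's own figure.** The point disputes no planned number, but 457 per arm serves as a denominator below, so it was reproduced first. Inputs from protocol 8.1 are 50% against 40%, two-sided 0.05, 80% power, 1:1 allocation and 15% dropout. With pooled variance and no continuity correction:

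n = [1.960 × √(2 × 0.45 × 0.55) + 0.842 × √(0.25 + 0.24)]² / 0.10² = 387.3, rounded up to 388.

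388 / 0.85 = 456.5, rounded up to 457; × 2 = 914. All three planned figures reproduce.

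**2. Safety set, rule by rule.**

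| Patient | Protocol 8.2 and abstract | SAP 3 |
|---|---|---|
| No dose | out | out |
| Exactly one dose, with a safety evaluation | **out** | **in** |
| Two or more doses, with a safety evaluation | in | in |
| Dosed, no safety evaluation | out | out |

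The documents part on the second row only. Three other places fit the SAP's threshold better. Protocol 8.5 tabulates events from the first dose onward. SAP 4.4.2 leaves out only events that start before the first dose. SAP 3 treats a single dose of test drug as enough exposure to move a control patient to the investigational group. Protocol 7.3.8 (pregnancy) itself uses a threshold of one dose or more.

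**3. Size for adverse event rates.** The documents do not say how many patients took exactly one dose. If 0.25% to 2% of an arm did (an assumption), that is about 1 to 9 of 457.

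For a rare event, protocol 1.3 gives allergy in 6 of 569 patients in the Japanese edaravone marketing trials: 6/569 = 1.05%, and 0.0105 × 457 = 4.8, about 5 patients. How many of these would stop after one dose is unknown:

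- none dropped: 5/457 = 1.09%
- one dropped: 4/456 = 0.88%, lower by 0.22 percentage points
- two dropped: 3/455 = 0.66%, lower by 0.43 percentage points

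For a commoner event, assume a true rate of 5% (22.85 expected of 457) and that every dropped patient had the event:

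- one dropped: 21.85/456 = 4.8%
- two dropped: 20.85/455 = 4.6%
- five dropped: 17.85/452 = 3.9%

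**4. Per-protocol set, truth table.**

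| Completed | Serious violation | With *or* | With *and* |
|---|---|---|---|
| yes | no | in | in |
| yes | yes | **in** | **out** |
| no | no | in | out |
| no | yes | out | out |

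The second row is the fault: it contradicts the list of deviations that follows the sentence. The third row is narrow, because dose intensity below 80% is itself listed. With 28 planned doses, 0.80 × 28 = 22.4, so only non-completers with 23 to 27 doses escape that item.

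**5. Efficacy.** The full analysis set is all randomised patients in both documents, so neither change touches the primary analysis, the sample size or alpha.

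**The case against.** The SAP already uses the one-dose threshold and grouping by drug received, and protocol 8.5 sends further safety detail to the SAP. The protocol phrase may be a translation slip for one or more. Both points stand, and they make the SAP wording the natural one to keep. They do not remove the conflict: the phrase appears twice in the protocol, no text found says which document prevails, and SAP 2.7 does not mention the difference. That entry lists no modification; it is not a positive statement that there was none.

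A reader might infer that requiring a safety evaluation removes patients who die or are lost straight after dosing. The documents do not support that. Neither says that the evaluation must be a scheduled visit, or that a death or event report fails to count. Deaths are serious adverse events reportable within 24 hours (protocol 7.3.1 and 7.3.7). The term is undefined, so a clarifying sentence is enough.

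A reader might also turn the allergy figure into a 20–40% fall in the rate. That needs 1 or 2 of about 5 reactors to stop after one dose, and no source gives that number. The 6 of 569 comes from another formulation and another population, with no timing, and this trial excludes known allergy.

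On the per-protocol set, the deviation list, the wrong-drug exclusion and the tabulated reasons for exclusion (SAP 4.2.1) show that violators were meant to be removed. It would go too far to say that the set cannot remove them, or that its membership is open until unblinding: protocol 9.1.3 requires analysable cases to be defined before lock, and protocol 5.4.1 puts the final unblinding after lock. The literal fault in the sentence remains.

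**Conclusion.** The point holds as two wording faults in set-membership rules. The safety set differs between protocol and SAP for patients with exactly one dose and a safety evaluation: out under the protocol, in under the SAP. The per-protocol *or* is not a conflict between the documents, since both carry it; read literally, it keeps completers with a serious violation and contradicts the listed exclusions.

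The effect on adverse event rates is unknown, because the documents give no count of one-dose patients. If about 1% of an arm had an allergic reaction, each reactor dropped would lower the rate by about 0.2 percentage points; if none stopped after one dose, the effect is zero. It should not be inferred that first-dose reactions will in fact be left out of the safety analysis: that follows only if the protocol wording overrides the SAP. The per-protocol set is secondary, so that part weighs less. The primary analysis is unaffected.

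**What to change.** - **Protocol 8.2 and abstract, safety set:** randomised patients who took at least one dose of study drug (active or placebo), analysed by drug received, to match SAP 3. Naming both products avoids doubt, because protocol 5.1 uses the term investigational product for the active tablet as distinct from the control.
- **Both documents:** state that any adverse event, serious adverse event or death recorded after dosing counts as a safety evaluation.
- **Protocol 8.2, abstract and SAP 3, per-protocol set:** change *or* to *and*. State how completion relates to the existing 80% dose-intensity item, so that patients with 23 to 27 doses are placed deliberately.
- **SAP 2.7:** record the difference in safety-set definition for as long as the protocol text stands.
- **Reporting:** give the number of patients per arm who took exactly one dose.

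The cost is wording and one extra count. The per-protocol set may become slightly smaller; the sample size and the primary analysis do not change.

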### **8.3. Baseline analysis**

Continuous variables were presented as median with interquartile range (IQR) and were compared with Wilcoxon test. Categorical variables were presented as frequency with proportion and were compared with chi-square test.

### **8.4. Efficacy analysis**

All the analyses were performed in the intention-to-treat population. Missing data on the primary outcome was imputed with treatment policy strategy, composite variable strategies, and while on treatment strategies accounting for intercurrent events, as follows:

- Treatment policy strategy

For the following concomitant events: After the subject is successfully randomized and starts to receive the treatment, concomitant medication/treatment is used during treatment (see Section 5.8) and the investigator does not discontinue the treatment or let the subject withdraw from the study early based on the actual situation; or the subject does not withdraw from the study early despite treatment delay, interruption or discontinuation due to AEs; the subject's mRS score can only be obtained remotely due to the pandemic, The primary efficacy outcomes will be treated by the treatment policy strategy, that is, regardless of whether the concomitant events occur. Whether the mRS reaches the standard will be assessed according to the measured mRS score collected (the mRS score of remote visit is considered valid).

- Composite strategy

For the following concomitant events: Randomized subjects, for whatever reason, do not have an mRS score after the start of the treatment;; or the main reason for the subject's early withdrawal from follow-up prescribed by the protocol is AE, the primary efficacy indexes will be treated by the composite strategy, i.e., the occurrence of such events is considered as

having a mRS score of 6 at the end of follow-up (Day 90 after treatment).

- While on treatment strategy

When a subject discontinues the treatment or withdraws from the study early for reasons other than those mentioned in the composite index strategy, the primary efficacy indexes will be treated by the while on treatment strategy, that is, using the most recent mRS score before the withdrawal from the study as the basis for determining whether the mRS meets the target.

Group difference in the primary efficacy outcome was examined using chi-square test or Fisher exact test, and the corresponding 95% confidence intervals (CIs) of the difference between proportions were estimated based on the normal-approximation. Odds ratios (ORs) with 95% CIs were calculated using logistic regression.

Unblinding sample size will be re-estimated in the interim analysis. If sample size adjustment occurs, the CHW method will be used to weight the test statistics in the final analysis, and the *P* value of the hypothesis testing will be estimated accordingly for statistical inference.

Similar approaches were used for binary secondary outcomes, including mRS score  $\leq 2$  on day 90, NIHSS score  $\leq 1$  on day 14, 30, and 90, and safety outcomes on adverse events and treatment related adverse events. For mRS score on day 90, an ordinal logistic regression analysis was performed, with the results presented as common OR and 95% CI, where a common OR in favor of Y-2 sublingual tablet was  $>1.0$ . For changes in NIHSS score from baseline to day 14, means with 95% CIs were calculated for each group, and the mean differences with 95% CI between the groups were estimated by generalized linear regression.

In addition, a post hoc sensitivity analysis was performed using different approaches to impute missing data on the primary efficacy outcome. Finally, the treatment effects on the primary outcome were analyzed among several prespecified subgroups by including the interaction between treatment and subgroup effect into the logistic regression model.

## **8.5. Safety analysis**

Data for safety evaluation include adverse events observed during the study and changes in laboratory data before and after treatment. Adverse event data are processed in statistical analysis after encoding according to the current version of MedDRA at the time of encoding.

Adverse events, adverse events during the study period since the first dose of the drug, major adverse events, unexpected adverse events, adverse event of special interest, serious adverse events, adverse events related to study drugs and serious adverse events related to study drugs are classified by system organ class and preferred term. Among them, significant adverse events are defined as adverse events that require drug therapy or non-drug therapy for the subject reporting the event; adverse events of special interest are divided into three types, i.e., liver function impairment, renal function impairment and hypokalemia. The Sponsor's clinical research associate is responsible for confirming and classifying all adverse events before unblinding.

If multiple adverse events occur in the same subject, the incidence rate is counted as 1 case; When the same AE occurs multiple times, the incidence of this AE is counted as 1. Adverse events will be summarized in frequency tables according to the system organ class (SOC) and preferred term (PT). The incidence is calculated by system, symptom/sign (count of cases: number of subjects who have experienced at least one adverse event).

The list of subjects experiencing adverse events and the list of subjects experiencing SAEs are provided. With respect to the laboratory data, in addition to the mean comparison before and after treatment, details of cases that are normal before treatment and abnormal after treatment or cases with abnormalities before treatment and abnormality exacerbation after treatment are mainly analyzed and listed. Refer to the statistical analysis plan for other details.

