|--------------|----------------------------|------------------|--|---|---|---|------------------|
| examinations | Hepatic and renal function | X  |  | X | X | X | X                |
|              | Myocardial enzyme          | X                |  | X | X | X | X                |
|              | Electrolytes               | X                |  | X | X | X | X                |
|              | Fasting blood glucose      | X  |  | X | X | X | X                |
|              | Blood lipid                | X                |  | X | X | X | X                |
|              | Coagulation function       | X                |  | X | X | X | X                |
|              | Homocysteine               | X                |  | X | X | X | X                |
|              | Electrocardiogram          | X                |  | X | X | X | X                |
|              | Pregnancy test             | X  |  |   |   |   | X  |
|              | Cranial CT                 | X                |  |   |   |   |                  |
|              | Cranial MRI                | X  |  |   |   |   |                  |
| Score        | mRS score                  | X  |  |   | X | X | X                |
|              | NIHSS score                | X                |  |   | X | X | X                |

|                                |                  |                  |   |   |  |  |
|--------------------------------|------------------|------------------|---|---|--|--|
| Parallel exploratory biomarker | X                |                  | X | X |  |  |
| SSS TOAST classification       |                  | X  |   |   |  |  |
| Randomization                  | X                |                  |   |   |  |  |
| Dosing                         |                  | X  |   |   |  |  |
| Concomitant medication         | X  |                  |   |   |  |  |
| Adverse event assessment       | X  |                  |   |   |  |  |

[1] Results of ALT, AST, and serum creatinine need to be obtained prior to randomization.

[2] Non-fasting state is allowed in the tests prior to treatment, indicating whether it's fasting or not.

[3] For women of childbearing age only.

[4] Optional and completed during the study. It is not a protocol deviation when the subject is unable to complete the MRI due to his/her own reasons.

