**6.1. Screening period (visit 1)**

- Informed consent form
- Demographics, including age, gender, height and weight (Height and weight information of subjects with unfavorable limbs can be obtained through interrogation);
- Disease attributes;
- Past medical history and medication, disease history and medication history before enrollment;
- Vital signs and physical examination, including heart rate, blood pressure, body temperature and respiratory rate. Physical examination is evaluated by organ and system;
- Blood routine, blood biochemistry (hepatic and renal function, blood glucose (non-fasting), blood lipids, myocardial enzyme, electrolytes and homocysteine), urine routine, coagulation function and ECG examination;
- Pregnancy test (for women of childbearing age only);
- NIHSS score; (If thrombolysis subjects have completed the NIHSS for screening period before thrombolysis, the pre-thrombolysis score should be used as the basis for enrollment)
- mRS score before this onset;
- Cranial CT (plain scan);
- Cranial MRI (optional and completed during the study);
- Randomization.

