**6.2. Treatment period****6.2.1. D7 ( $\pm 1$ ) (visit 2)**

- Vital signs and physical examination (including weight)
- Blood routine, blood biochemistry (Hepatic and renal function, blood glucose (fasting), blood lipids, myocardial enzyme, electrolytes and homocysteine), urine routine, coagulation function and ECG examination

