#### **4.4.4 Vital Signs and Laboratory Test Examination**

Within each treatment group, the number and percentage of subjects with elevated in vital signs from baseline to day 14 after randomization will be described and Fisher’s Exact test will be used to compare the difference between treatment groups. The baseline measurements and changes after treatment of blood routine and bloodbiochemistry will be described as "abnormal and clinically significant" will be determined by the researchers. Within each treatment group, the number and percentage of subjects with an "abnormal and clinically significant" value will be summarized and Fisher’s Exact test will be used to compare the difference between treatment groups.

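### Glucose may be non-fasting at baseline but is fasting at every later visit, and the planned change and shift summaries ignore the recorded fasting state

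*Combined protocol and SAP*

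**What the plan says.** **Sampling.** Protocol 6.1 (Visit 1) lists the biochemistry panel with "blood glucose (non-fasting), blood lipids, myocardial enzyme, electrolytes and homocysteine". Protocol 6.2.1 (Day 7) lists "blood glucose (fasting), blood lipids, myocardial enzyme, electrolytes and homocysteine", and Sections 6.2.2, 6.3.1 and 6.3.2 give the same fasting condition at Days 14, 30 and 90. In the Section 6 flow chart the row is headed as fasting glucose, and footnote [2] to its baseline cell reads "Non-fasting state is allowed in the tests prior to treatment, indicating whether it's fasting or not".

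**Baseline.** SAP 4.1.3, item 3, takes the last available value before the first dose and sets no fasting condition.

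**Analysis.** Protocol 2.2.3 makes within-group laboratory change a safety outcome. Protocol 8.5 provides "in addition to the mean comparison before and after treatment, details of cases that are normal before treatment and abnormal after treatment"; the same sentence goes on to list patients who were already abnormal and got worse. SAP 4.4.4 says that "The baseline measurements and changes after treatment of blood routine and" blood biochemistry will be described. It then counts, by arm, patients with values that the investigator judges abnormal and clinically important, and compares those counts with Fisher's exact test. None of these sections refers to the fasting state that footnote [2] asks sites to record.

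**The concern.** For any patient with a non-fasting baseline, the sampling condition changes at the same moment as treatment starts. A before/after difference in glucose then contains the loss of the meal effect as well as whatever the drug, the recovery from the acute stroke and concomitant treatment contribute. A patient whose fasting glucose is normal but whose baseline sample followed a meal can be classed as abnormal before treatment, and so cannot enter the normal-to-abnormal listing.

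At stake is whether the glucose rows of a stated safety outcome can be read. A fall in mean glucose in the active arm could be taken as reassuring when part or all of it is a sampling artefact, and a real rise could be partly masked within the arm. The primary endpoint, the power and the type I error are not touched.

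**Working it through.** **Inputs from the documents.** Visit 1: non-fasting listed (6.1), non-fasting allowed and state recorded (footnote [2]). Visits 2 to 5: fasting. Baseline definition and analyses: no fasting condition. The documents give no glucose values, no share of non-fasting baselines and no reference limit, so there is no figure of the plan's own to reproduce.

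**Step 1, within-arm mean.** Let X0 be the fasting level at baseline, X1 the fasting level at follow-up, f the share of baselines that are non-fasting and m the average meal increment among them. The recorded baseline has mean X0 + f × m, so

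mean recorded change = mean(X1 − X0) − f × m.

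With no true change the result is −f × m. It is zero when f = 0.

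**Step 2, between-arm mean.** The fasting state is fixed before the first dose in a randomised, double-blind trial, so f and m are the same in both arms in expectation:

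(change in active − f × m) − (change in placebo − f × m) = change in active − change in placebo.

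The difference in mean change is not biased.

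**Step 3, shifts.** Let U be the upper limit, and assume that the same limit is applied to fasting and non-fasting samples (the documents do not say). A true normal-to-high shift has X0 ≤ U and X1 > U. It leaves the normal-to-abnormal listing when X0 + meal increment > U. It then appears in the abnormal-and-worse listing if X1 exceeds the recorded baseline, and in neither listing if X1 lies between U and the recorded baseline.

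By hand, on assumed values in mmol/L: fasting level 5.8, limit 6.1, true rise 1, so follow-up is 5.8 + 1 = 6.8, a true shift. With a meal increment of 1 the recorded baseline is 6.8 and the recorded change 6.8 − 6.8 = 0. With an increment of 3 the recorded baseline is 8.8 and the recorded change 6.8 − 8.8 = −2.0. In both cases the patient is abnormal before, not worse after, and in neither listing.

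**Step 4, range under assumptions.** A simulation of 400,000 patients per scenario used fasting levels in units of the between-patient SD, a baseline to follow-up correlation of 0.7 and an upper limit at +1 SD. The second and third result columns assume no drug effect. The last two assume a rise of 0.30 SD in the active arm only. These are illustrations, not estimates for this trial.

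| Non-fasting share, f | Meal increment, m (SD) | Mean within-arm change (SD) | Normal-to-high shifts absent from that listing | Arm difference in shift rate, points: all fasting → as recorded | Arm difference in mean change (SD) |
|---|---|---|---|---|---|
| 0% | 0.25 | 0.00 | 0% | 6.0 → 6.0 | 0.30 |
| 25% | 0.25 | −0.06 | 7% | 6.0 → 5.7 | 0.30 |
| 50% | 0.5 | −0.25 | 25% | 5.9 → 4.8 | 0.30 |
| 100% | 1.0 | −1.00 | 82% | 5.9 → 1.8 | 0.30 |

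The third column agrees with −f × m (for example −0.5 × 0.5 = −0.25). The fourth column counts every shift that leaves the normal-to-abnormal listing, including those that would move to the abnormal-and-worse listing.

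**The case against.** The strongest reply is that randomisation and blinding already deal with this. Both arms are sampled under the same rules, and the only laboratory test in SAP 4.4.4 compares arms on clinically important abnormal values, a count that states no need for a normal baseline. Protocol 8.5 also lists abnormal-and-worse cases, and Protocol 7.2.2 sends clinically relevant laboratory changes to the adverse event pages. Glucose is not among the adverse events of special interest, which cover liver, kidney and low potassium. Even a fasting baseline would not isolate a drug effect within an arm, because it is taken within 48 hours of stroke onset and Protocol 5.8.1 allows glucose-lowering treatment.

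Most of that stands, and it is why the weight is small. It is not a full answer. The outcome in Protocol 2.2.3 is defined within each group, which is where the artefact falls. SAP 4.4.4 only describes mean laboratory change, so the unbiased contrast of Step 2 is not a planned comparison. Where shift counts are set side by side, arm differences are pulled toward zero rather than merely made noisier.

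Two stronger readings are tempting. A reader of Section 6.1 alone might infer that every baseline is non-fasting, so that a fall is built in. Footnote [2] only permits a non-fasting sample and has the state recorded, so baseline may be a mix in unknown proportion. A reader might also infer that triglycerides are affected, since lipids stand next to glucose in the panel. The fasting qualifier is attached to glucose alone, no visit gives a fasting state for lipids, and no section says that they share a draw.

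**Conclusion.** The mismatch is documented for glucose, and no planned analysis uses the flag that would resolve it. To the extent that baselines are non-fasting, within-arm glucose change is shifted downward in both arms by f × m, some normal-to-high shifts are missed or relisted as abnormal-and-worse, and arm differences in shift rate are attenuated. The shift part rests on one upper limit being used for both fasting states.

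The size for this trial cannot be stated. It is zero if all baselines are fasting and otherwise depends on a share and an increment that the documents do not give. It would go too far to say that the plan hides glucose rises, because the abnormal-and-worse listing and the count of clinically important values can still catch part of them. It would also be wrong to say that the comparison of mean change between arms is biased. This is a minor point about one analyte in a descriptive safety summary, worth correcting because the remedy is cheap.

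**What to change.** In Protocol 8.5 and SAP 4.4.4, for glucose only:

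1. Present the change-from-baseline and shift tables by recorded baseline fasting state (fasting, non-fasting, not recorded), and read within-arm change only from the fasting-baseline stratum.
2. Summarise the fasting values at Days 7, 14, 30 and 90 by arm for all patients with a value, without reference to baseline.
3. Reconcile Section 6.1, which lists the Visit 1 sample as non-fasting, with footnote [2], which allows it.

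The cost is a few lines of analysis wording; no visit or sample changes, because footnote [2] already asks for the state. The downside is a smaller fasting-baseline stratum, whose size is not known from the documents. Its within-arm change will still reflect recovery from the acute stroke and concomitant treatment, so it should be read with the two arms side by side.
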